### Outcome measurement

#### Primary outcome

The primary study outcome will be the time to first bowel sound recovery following surgery, defined as the first time point at which the bowel sounds are heard by GCP-trained nurses at three consecutive time points. The judgment of bowel sounds is based only on the results of auscultation by GCP-trained nurses, even if some patients may feel residual colon gas discharge early after surgery.

#### Secondary outcomes

##### Postoperative recovery of gastrointestinal function

Measured variables for this outcome include: water intake time (the time of first water intake after operation), solid food tolerance time (solid food tolerance indicates that there is no nausea or vomiting within 4 h after a meal), first anal exhaust time, the time at which the patient is able to leave the bed, and the use of gastrointestinal functional adjuvant medicines.

##### Postoperative pain treatment

Recorded variables for this outcome include: the pain intensity score as measured by NRS; analgesia-related side effects; cumulative analgesic drug doses; and the use of PCIA at 9:00 a.m. and 3:00 p.m. on the 1st, 2nd, and 3rd days after operation. Analgesia-related side effects include: respiratory depression, excessive sedation, urinary retention, and pruritus.

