#### Exclusion criteria

Patients meeting any of the following criteria will be excluded from this trial: scars or sensory impairments around the acupoints of interest; infections around the acupoints of interest; peripheral nerve injuries; history of spinal surgery; participation in other clinical trials within the past 4 weeks; inability to understand Numeric Rating Scales (NRS) scores or rejection of patient-controlled intravenous analgesia (PCIA); patients with a cardiac pacemaker; females in periods of menstruation, pregnancy, or breastfeeding; patients with preoperative pain or a history of analgesic usage; patients with mental or neurological diseases; patients who require an intraoperative colostomy; heavy drinking, defined by the National Institute on Alcohol Abuse and Alcoholism as more than three standard drinks (containing 14 g of pure alcohol) per day for women and more than four standard drinks per day for men [22]; patients returning to the intensive care unit; patients with allergies or a history of steroid usage; patients who develop serious intraoperative complications will be excluded after operation (such as blood loss > 2000 ml; brain, heart, and lung-related complications); patients with a history of liver or kidney disease; serum K^+^ > 5.5 mmol/L or < 3.0 mmol/L; preoperative hemoglobin < 7 g/dl; or patients deemed unsuitable by the researchers.

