### Interventions

For this study, the bilateral Hegu (LI4), Neiguan (P6), Zusanli (ST36), and Sanyinjiao (SP6) acupoints will be selected. A HANS 100B (four conductors, eight electrodes) transdermal acupoint electrical stimulation apparatus (Nanjing Jisheng Company) will be used to stimulate the bilateral Hegu (LI4) and Neiguan (P6) acupoints for 30 min before anesthetic induction and during the intraoperative period until suturing of the surgical site is completed. The Hegu (LI4), Neiguan (P6), Zusanli (ST36), and Sanyinjiao (SP6) acupoints will be stimulated at 9:00 a.m. and 3:00 p.m. each day on the 1st, 2nd, and 3rd postoperative days. Each treatment will last for 30 min. Stimulation parameters will be as follows: a dense-disperse frequency of 2/100 Hz, with true stimulation being the maximum tolerable setting for a patient, and with sham simulation being 1 mA lower than the current that patients are able to just feel. The test groups for Part 1 are presented in Table 1, and a study design flowchart is shown in Fig. 1.

**Table 1 Tab1:** Part 1 test groups

Group	Sample size (*n*)	Intervention
Con	80	Sham TEAS before, during, and after operation
T1	120	Preoperative and intraoperative TEAS, and postoperative sham TEAS
T2	80	Preoperative TEAS, intraoperative sham TEAS, and postoperative TEAS
T3	120	TEAS before, during, and after operation

*TEAS* transcutaneous electrical acupoint stimulation

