**Fig. 1 Fig1:**
[figure not shown]
Part 1 trial flowchart. For group details, see Table 1. d days, TEAS transcutaneous electrical acupoint stimulation

Preliminary data analysis based on Part 1 suggest potential benefits of postoperative TEAS for gastrointestinal function recovery, but the effect was slight. Previous animal experiments have suggested that 5 Hz is more effective than 2/100 Hz as a means of promoting the recovery of gastrointestinal function, so we will adjust the study stimulation frequency before initiating Part 2 of this study protocol. In Part 2, all patients will be stimulated at 2/100 Hz (Hegu (LI4) and Neiguan (P6) acupoints; bilateral) before and during surgery. After surgery, patients will receive no TEAS, sham TEAS, 5-Hz TEAS, or 100-Hz TEAS. The same acupoints will be assessed in this trial. In order to observe colorectal function recovery more specifically, Part 2 of this study will focus only on patients undergoing colorectal surgery. The test groups for Part 2 of this study are presented in Table 2, with a study design flowchart shown in Fig. 2.

**Table 2 Tab2:** Part 2 test groups

Group	Sample size (*n*)	Intervention		
		Preoperative	Intraoperative	Postoperative
Con′	100	2/100 Hz TEAS	2/100 Hz TEAS	Control
T1′	100	2/100 Hz TEAS	2/100 Hz TEAS	Sham TEAS
T2′	100	2/100 Hz TEAS	2/100 Hz TEAS	5 Hz TEAS
T3′	100	2/100 Hz TEAS	2/100 Hz TEAS	100 Hz TEAS

*TEAS* transcutaneous electrical acupoint stimulation

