### Sample size calculations

This study utilizes a superiority design, and the sample size has been calculated according to the primary endpoint of time to first bowel sound recovery following surgery. Based on a single-center preliminary test, this recovery time was 60.320 ± 9.8167 h in sham TEAS-treated individuals and 51.558 ± 17.8499 h in patients who received TEAS during all phases of the perioperative period. Therefore, the difference between the two groups was 8.762 h. Adopting a conservative point of view, the larger standard deviation of 17.8 was used to calculate the optimal sample size. In Part 1, according to a ratio of 3:2 and a power of 90%, a total of 110 and 73 patients were needed per group. To additionally account for a 10% drop-out rate, these case numbers were increased to 120 and 80, respectively. The reason for this unbalanced design between the groups was that both the T1 and T3 groups underwent TEAS before and during the operation, and thus have the potential to achieve a better therapeutic outcome. To ensure maximal possible patient protection, 80 cases were included in the Con and T2 groups, while 120 cases were included in the T1 and T3 groups.

In Part 2, as all patients received the same preoperative and intraoperative interventions, the allocation ratio was altered to 1:1:1:1, with 100 participants per group.

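### In Part 2, analgesic use before the first postoperative session, and possibly the 09:00 day-1 readings, cannot differ by allocation; the stated unadjusted tests leave this information unused and lose precision on secondary outcomes

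*Protocol article*

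**What the plan says.** All references are to the protocol article.

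- **What is randomized in Part 2.** Sample size calculations: "In Part 2, as all patients received the same preoperative and intraoperative interventions, the allocation ratio was altered to 1:1:1:1, with 100 participants per group". The Part 2 text under Interventions: "After surgery, patients will receive no TEAS, sham TEAS, 5-Hz TEAS, or 100-Hz TEAS". Table 2 shows the same 2/100 Hz stimulation before and during surgery in all four arms.
- **When postoperative treatment starts.** Interventions says the acupoints "will be stimulated at 9:00 a.m. and 3:00 p.m. each day on the 1st, 2nd, and 3rd postoperative days", and "Each treatment will last for 30 min". This stands with the Part 1 regimen and is not restated for Part 2.
- **When opioid use starts.** The PCIA pump is connected at the end of surgery, before transfer to the PACU.
- **What is recorded.** Besides NRS pain and side effects, Postoperative pain treatment lists "cumulative analgesic drug doses; and the use of PCIA at 9:00 a.m. and 3:00 p.m. on the 1st, 2nd, and 3rd days after operation". Nausea is scored at the same two clock times on days 1 to 5. Acupuncture-balanced anesthesia efficacy adds an NRS pain score after extubation, and nausea and vomiting during recovery.
- **How groups are compared.** Statistical analysis names ANOVA or Kruskal–Wallis. Primary/secondary efficacy endpoints describes an ANCOVA with a baseline term, but its dependent variable is the primary endpoint, and no baseline is named for pain or nausea.
- **Preoperative pain.** Exclusion criteria remove "patients with preoperative pain or a history of analgesic usage".

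**The concern.** The outcome list serves both parts and was not adapted to Part 2, where only the postoperative treatment differs. Whatever happens before the first postoperative session is, for the Part 2 contrast, pre-treatment information. If analgesic doses are counted from surgery, a block of opioid use that allocation cannot affect enters the outcome and adds variance. The same block, used as a covariate, would remove variance. The 09:00 day-1 scores may be in the same position, since reading and session share a clock time. A preoperative pain score could not do this job, because patients with preoperative pain are excluded. At stake is the precision of the Part 2 pain, nausea and analgesic comparisons.

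**Working it through.** **The plan's own figure.** The only computed sample size is for the primary endpoint in Part 1: difference 8.762 h, SD 17.8 h, two-sided 0.05, 90% power, ratio 3:2. The smaller group is (1 + 1/1.5) × [17.8 × (1.960 + 1.282)/8.762]² = 72.3, so 73; 1.5 × 73 = 109.5, so 110. Both stated figures reproduce, and this point does not touch them.

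**Assumed inputs.** The article gives no SD, correlation or effect for pain, nausea or analgesic dose, so everything below is illustrative. Power is for one pairwise comparison at 100 per arm, two-sided 0.05: Φ(δ/(σ√(2/100)) − 1.96).

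**1. Time before the first session.** From 09:00 on day 1 to 15:00 on day 3 is 54 h. If surgery ends at 12:00 / 15:00 / 18:00, the earlier period is 21 / 18 / 15 h out of 75 / 72 / 69 h, that is 28% / 25% / 22%.

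**2. Analgesic dose.** Let k be the SD of the pre-session dose over the SD of the on-treatment dose, and r their correlation. If the SD is proportional to the length of the period, surgery ending at 15:00 gives k = 18/54 = 1/3. Relative to the on-treatment dose:

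- variance of the from-surgery total: 1 + k² + 2rk
- variance after adjusting for the pre-session dose: 1 − r²

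| r | Total, unadjusted | On-treatment, unadjusted | On-treatment, adjusted | Adjusted / total |
|---|---|---|---|---|
| 0.3 | 1.311 | 1 | 0.91 | 0.694 |
| 0.5 | 1.444 | 1 | 0.75 | 0.519 |
| 0.7 | 1.578 | 1 | 0.51 | 0.323 |

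The combined reduction is 31% / 48% / 68%. Removing the pre-session dose alone gives 1 − 1/(1 + k² + 2rk) = 24% / 31% / 37%; adjustment supplies the rest. Over surgery ends from 12:00 to 18:00, the SD of the total exceeds that of the on-treatment dose by 11% to 30%. For an assumed effect of 0.4 on-treatment SD (k = 1/3), power is 70% / 65% / 62% for the total, 81% for the on-treatment dose, and 84% / 90% / 98% adjusted. The absolute group difference is the same in all three.

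**3. Scores tested one time point at a time.** If the 09:00 day-1 score is taken before the session, adjustment leaves 1 − r² = 0.91 / 0.75 / 0.51 of the variance. For a 0.3 SD effect, unadjusted power is Φ(0.3/0.1414 − 1.96) = 56%. Dividing 0.3/0.1414 by √(1 − r²) gives 60% / 69% / 84%.

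**4. Scores averaged over time.** No averaging is stated, so this is a separate scenario. With equal correlation ρ between all readings, a constant 0.3 SD effect after the first reading, and that reading untreated, the mean of all K readings keeps (K − 1)/K of the effect: 5/6 for pain (taking the clock times to cover NRS), 9/10 for nausea. Power at ρ = 0.3 / 0.5 / 0.7:

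| | All readings | First dropped | First as covariate |
|---|---|---|---|
| Pain (K = 6) | 78 / 64 / 53% | 89 / 78 / 68% | 95 / 95 / 98% |
| Nausea (K = 10) | 88 / 73 / 61% | 93 / 81 / 70% | 98 / 97 / 99% |

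Equal correlation is a favourable assumption. If correlation with the first reading fades over the days, the covariate gains less.

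**The case against.** The strongest objection is that this is a condensed article, and that summary measures, accumulation windows and covariates for secondary outcomes are commonly left to an analysis plan. That stands for much of the analysis detail. It does not cover the order of reading and session, which no analysis plan can recover afterwards, and the tests the article does name are unadjusted.

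A reader might also infer more than the text supports:

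- **That the 09:00 day-1 scores precede treatment.** The order is not given. A reading taken during or after the session reflects at most one 30-minute session. In the pain section the clock times may even belong to PCIA use only.
- **That cumulative dose is counted from surgery.** No start is stated.
- **That the comparisons are diluted.** For scores this needs pooling over time points, which is not specified. For dose, the absolute difference is unchanged; noise rises and the relative difference shrinks.
- **That the 09:00 day-1 reading is the only usable baseline.** The post-extubation NRS and the recovery-period nausea record also precede Part 2 postoperative treatment.

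Two further points stand. Once the pre-session dose is a linear covariate, analysing the total or the on-treatment dose gives the same treatment estimate and residual variance, so adjustment is the essential step. In Part 1 several arms differ before or during surgery, so early opioid use is a genuine outcome there.

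**Conclusion.** The point holds as lost precision on Part 2 secondary outcomes. It is neither bias nor a contradiction, and it leaves the primary endpoint and its sample size untouched. The firm part is that analgesic use between the end of surgery and the first postoperative session carries no randomized contrast. That start is 09:00 on day 1, provided the schedule under Interventions carries over to Part 2, a reasonable reading that the article does not restate. The 09:00 day-1 readings may share this status. The size is not fixed by the document: 31% to 68% less variance for analgesic dose and 9% to 49% for a single later score (1 − 0.91 to 1 − 0.51), both over correlations of 0.3 to 0.7 and the other assumptions above. Adjustment gains precision at every correlation tried.

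**What to change.** For Part 2:

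1. State whether the postoperative session times under Interventions apply. For patients still to be enrolled, take the 09:00 day-1 pain, nausea and PCIA readings immediately before the first session.
2. Analyse analgesic consumption from that reading to 15:00 on day 3 by ANCOVA, adjusted for use up to the first session. Keep the from-surgery total as a descriptive figure.
3. Analyse the later pain and nausea readings by ANCOVA, adjusted for the 09:00 day-1 score where it was taken before the session. Otherwise use the post-extubation NRS or the recovery-period nausea record. A score taken after the session must not be the covariate, because it may already carry part of the effect.

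For Part 1, recruitment and analysis are finished according to Trial status, so the same approach to T3 versus T1, which differ only after surgery, could be supplementary only.

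The cost is a bedside instruction on the order of reading and session plus analysis wording. No new measurement is needed, and each score loses one outcome time point. The instruction cannot reach patients already measured, and recruitment was expected to end in July 2019; adjustment for values already collected remains possible for everyone.

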##### Acupuncture-balanced anesthesia efficacy

Recorded variables for this outcome include: respiratory and circulatory function during and after operation, depth of anesthesia, dosage of anesthetics and analgesics during induction and intraoperative maintenance, respiratory recovery time after operation, anesthesia recovery time, extubation time, occurrence of restlessness, nausea and vomiting during the recovery period, and NRS pain scores after extubation.

##### Postoperative nausea and vomiting

Recorded variables for this outcome include: the degree of nausea, as scored by NRS (0–10 points). This variable will be scored at 9:00 a.m. and 3:00 p.m. on days 1–5 post operation, and instances of vomiting will also be recorded. 5-HT_3_ receptor antagonists will be given for nausea scores ≥ 7 or when patients vomit ≥ 1 time.

##### Postoperative complications

Recorded variables for this outcome include: postoperative instances of heart, lung, and brain complications.

##### Quality of life assessment

The SF-8 questionnaire will be used to assess quality of life before the operation and 1 month after discharge.

##### Immunological and inflammatory indexes

Immunological and inflammatory indexes include: preoperative and postoperative blood cortisol levels, ACTH, TNF-α, IL-1β, and changes in adaptive immune cells (T cells, B cells, DCs).

We may further examine and analyze these patients’ prognosis.

The SPIRIT figure is shown in Fig. 3, Additional files 3 and 4.

**Fig. 3 Fig3:**
[figure not shown]
Standard Protocol Items: Recommendations for Interventional Trials (SPIRIT) figure. For group details, see Tables 1 and 2. GI gastrointestinal, PONV postoperative nausea and vomiting, QOL quality of life

### Sample size calculations

This study utilizes a superiority design, and the sample size has been calculated according to the primary endpoint of time to first bowel sound recovery following surgery. Based on a single-center preliminary test, this recovery time was 60.320 ± 9.8167 h in sham TEAS-treated individuals and 51.558 ± 17.8499 h in patients who received TEAS during all phases of the perioperative period. Therefore, the difference between the two groups was 8.762 h. Adopting a conservative point of view, the larger standard deviation of 17.8 was used to calculate the optimal sample size. In Part 1, according to a ratio of 3:2 and a power of 90%, a total of 110 and 73 patients were needed per group. To additionally account for a 10% drop-out rate, these case numbers were increased to 120 and 80, respectively. The reason for this unbalanced design between the groups was that both the T1 and T3 groups underwent TEAS before and during the operation, and thus have the potential to achieve a better therapeutic outcome. To ensure maximal possible patient protection, 80 cases were included in the Con and T2 groups, while 120 cases were included in the T1 and T3 groups.

In Part 2, as all patients received the same preoperative and intraoperative interventions, the allocation ratio was altered to 1:1:1:1, with 100 participants per group.

### Statistical analysis

Continuous variables will be expressed as: mean (SD), median (interquartile range (IQR)), or minimum and maximum. For comparisons between treatment groups, analyses of variance (ANOVAs) will be used for normally distributed variables, and the Kruskal–Wallis *H* test will be used for non-normally distributed variables. Categorical variables will be expressed as numbers (%), and will be analyzed via chi-square tests for between-group comparisons.

Statistical significance for this study is defined as α = 0.05 for a two-sided test. *P* values will be rounded to three decimal places; values below 0.001 will be reported as < 0.001. Statistical analyses will be conducted using SAS version 9.4 (SAS Institute Inc.).

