Patients and their families will be taught how to record postoperative diaries before study initiation, including time of water intake, solid food tolerance, first anal exhaust, and the time at which the patient is first able to leave bed. These diaries will be returned to researchers on the 5th day after operation.

Analgesics will be administered as follows: when the pain NRS score is ≥ 4 even after five consecutive effective bolus applications of the PCIA pump, 50 mg pethidine will be given intramuscularly.

PONV will be treated as follows: nausea levels will be scored via NRS (0–10; 0 for no nausea, 10 for intolerable nausea). 5-HT_3_ receptor antagonists will be given for nausea scores ≥ 7 or when patients vomit more than once. Rescue medication including pethidine and 5-HT_3_ receptor antagonists will be recorded in the remedial tables.

Venous blood (5 ml) will be collected both at the preoperative stage prior to TEAS and 4–5 days after operation. The blood samples will be sent to the Department of Immunology of Peking University Medical Department for immunological and inflammatory index measurements.

When an adverse event occurs, the observer will be able to decide whether to discontinue the observation based on the patient’s condition. If serious adverse events occur, the researchers will immediately take necessary measures to ensure the safety of the patients. All adverse events will be tracked and carefully recorded until the subjects are stable. Those with abnormal laboratory examinations of clinical significance will be monitored until readings return to pretreatment levels.

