### Primary/secondary efficacy endpoints

A covariance model (ANCOVA) will be fitted, with primary endpoint changes from baseline serving as the dependent parameter, and with treatment group, baseline, and study site serving as fixed effects for consideration of site–treatment interactions. For ordinal and categorical variables, a Cochran–Mantel–Haenszel (CMH) test will be used, with study site as a stratifying factor.

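### SF-8 and the blood immune and inflammatory indexes have preoperative values, but no sentence clearly applies baseline adjustment to them, and the only ANCOVA names an endpoint that has no baseline

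*Protocol article*

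**What the plan says.** Two families of secondary outcomes are measured before and after surgery.

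- **Quality of life** (Quality of life assessment): "The SF-8 questionnaire will be used to assess quality of life before the operation and 1 month after discharge".
- **Blood indexes** (Immunological and inflammatory indexes): "preoperative and postoperative blood cortisol levels, ACTH, TNF-α, IL-1β, and changes in adaptive immune cells". The sampling times are under Interventions: "Venous blood (5 ml) will be collected both at the preoperative stage prior to TEAS and 4–5 days after operation".

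Two places describe how continuous variables are compared between arms.

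- **Statistical analysis** gives a general rule: "analyses of variance (ANOVAs) will be used for normally distributed variables, and the Kruskal–Wallis *H* test will be used for non-normally distributed variables". It mentions no covariate.
- **Primary/secondary efficacy endpoints** describes an ANCOVA "with primary endpoint changes from baseline serving as the dependent parameter, and with treatment group, baseline, and study site serving as fixed effects". Its next sentence gives a Cochran–Mantel–Haenszel test, stratified by study site, for ordinal and categorical variables.

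No sentence names the model for SF-8 or for any blood index.

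**The concern.** The one baseline-adjusted model is attached by name to an endpoint that cannot have a baseline. Time to first bowel sound is counted from surgery, so no change from a preoperative value exists. The outcomes that do have a preoperative value are not named in that model. Taken literally, they fall under the general rule of unadjusted ANOVA or Kruskal–Wallis.

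Two things would follow. Standard errors would be larger than the collected data allow whenever baseline and follow-up are correlated. Any chance difference between arms at baseline would also carry over into the follow-up comparison.

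Exploring neuroimmune–endocrine mechanisms is a stated aim, and the blood indexes are the listed outcomes that measure it directly. SF-8 is the only quality-of-life instrument.

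**Working it through.** **1. The plan's own figure.** The only stated sample size concerns the primary endpoint: "according to a ratio of 3:2 and a power of 90%, a total of 110 and 73 patients were needed per group". Inputs from Sample size calculations and Statistical analysis: difference 8.762 h, SD 17.8 h, power 90%, ratio 3:2, two-sided α 0.05.

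Smaller arm = (1 + 1/1.5) × (1.960 + 1.282)² × (17.8/8.762)² = 1.667 × 10.51 × 4.127 ≈ 72.3, so 73. Larger arm = 1.5 × 73 = 109.5, so 110.

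The figure reproduces, but it says nothing about SF-8 or the blood indexes. The article gives no effect size, power or correlation for them.

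**2. Precision with and without the baseline.** Let rho be the correlation between the preoperative and follow-up values, with equal variance at both times. Relative to comparing follow-up values alone:

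- ANCOVA with baseline as covariate: variance factor 1 − rho²
- unadjusted change score: variance factor 2(1 − rho)
- equivalent arm size for a Part 2 arm of 100 under ANCOVA: 100/(1 − rho²)

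| rho (assumed) | ANCOVA factor | Variance saved | Unadjusted change factor | Arm of 100 acts like |
|---|---|---|---|---|
| 0.2 | 0.96 | 4% | 1.6 | 104 |
| 0.3 | 0.91 | 9% | 1.4 | 110 |
| 0.5 | 0.75 | 25% | 1.0 | 133 |
| 0.7 | 0.51 | 49% | 0.6 | 196 |

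An unadjusted change score is never more precise than ANCOVA, and below rho = 0.5 it is worse than ignoring the baseline.

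**3. What this means for power (illustrative).** Take an effect that an unadjusted two-arm comparison would detect with 80% power: (1.960 + 0.842) × √(2/100) = 0.396 SD at 100 v 100. Adjusted power = Φ(2.802/√(1 − rho²) − 1.960).

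- rho 0.2: 81.6%
- rho 0.3: 83.6%
- rho 0.5: 89.9%
- rho 0.7: 97.5%

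Allowing 10% drop-out (90 v 90), an assumed effect of 0.4 SD and a noncentral t calculation, power is 76.1% unadjusted. It becomes 79.9%, 86.9% and 96.2% at rho 0.3, 0.5 and 0.7.

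**4. Chance imbalance.** If two arms differ by b SDs at baseline, the unadjusted follow-up difference shifts by about rho × b SDs. With b = 0.2 and rho = 0.5 (both assumed), the shift is 0.1 SD. Randomisation makes this zero on average, but not in the trial at hand.

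**5. The two passages side by side.** If the ANCOVA covers only what it names, the general rule governs SF-8 and the blood indexes. If it is meant to cover secondary endpoints too, the two sections give different tests for the same variables, with no rule for choosing between them. On either reading the text does not settle the analysis.

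**The case against.** A reader might infer that the plan deliberately reserves baseline adjustment for the primary endpoint and commits SF-8 and the blood indexes to unadjusted tests. The article does not support that, for four reasons.

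- The ANCOVA sits under a heading that covers secondary endpoints. The Cochran–Mantel–Haenszel sentence beside it cannot concern a primary endpoint measured in hours, so the section does reach secondary outcomes.
- A change-from-baseline model is impossible for time to first bowel sound but fits SF-8 and the blood indexes, so the authors may have had such outcomes in mind.
- The Missing data section provides for imputing missing baseline values, which suggests that baselines were meant to be used.
- No sentence says that follow-up values alone will be tested. The wording for immune cells refers to changes.

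A reader might also object to change as the dependent variable. That does not hold for the model as written: change with baseline as a covariate gives the same treatment estimate and standard error as ANCOVA on the follow-up value. The 2(1 − rho) penalty applies only to change scores tested without that covariate.

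The sizes have no anchor in the article. Nothing in it supports a particular correlation between a preoperative assay and one taken 4–5 days after surgery, or between SF-8 before surgery and 1 month after discharge. At rho 0.2 to 0.3 the power gain is only about 1 to 4 points.

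Finally, covariates for individual secondary outcomes are often left to a statistical analysis plan. That would answer a complaint about silence. Here the article states one test for continuous variables and a different model under secondary endpoints, and names the wrong kind of outcome in the latter. That part of the concern stands.

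**Conclusion.** The point holds as a minor ambiguity with a useful and nearly free correction. The article does not clearly apply baseline adjustment to outcomes whose baselines it collects, and the only sentence that adjusts for baseline names an endpoint without one.

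If the general rule were followed literally on follow-up values, the loss would be a fraction rho² of the variance: small at rho 0.2 to 0.3 and material from about 0.5. These sizes rest on an assumed rho, and the power figures also on an assumed effect. They illustrate the scale and do not measure a loss in this trial. If the ANCOVA was meant to cover these outcomes, no precision is lost and only the wording needs repair.

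Only secondary outcomes are involved. The primary conclusion does not depend on this point.

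**What to change.** In Primary/secondary efficacy endpoints, state that SF-8 at 1 month and each postoperative cortisol, ACTH, TNF-α, IL-1β and immune-cell value is analysed by ANCOVA on the follow-up value (equivalently, change with baseline as covariate). The covariates are the patient's own preoperative value, treatment group and study site, plus the gastric or colorectal stratum in Part 1. Log-transform skewed assay values at both times, or use rank ANCOVA where a transformation is inadequate. Do not test change scores without the baseline covariate. Keep ANOVA and Kruskal–Wallis for outcomes with no baseline, and stop describing the primary endpoint as a change from baseline.

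The article says Part 2 is still recruiting, so this can be set before its analysis. Part 1 has been analysed, so any adjusted analysis there should be labelled as added. The cost is a sentence or two and a little extra programming, with no new data, visits or patients.

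### The pilot SDs differ by a variance ratio of 3.3, but the stated ANOVA and ANCOVA assume one common variance; if that gap carries over, Part 1 contrasts on a four-arm pooled error are misstated in both directions

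*Protocol article*

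**What the plan says.** The Sample size calculations section of the protocol article reports a pilot in which "this recovery time was 60.320 ± 9.8167 h in sham TEAS-treated individuals". The corresponding figure for the other pilot arm was "51.558 ± 17.8499 h in patients who received TEAS during all phases of the perioperative period". For sizing, "the larger standard deviation of 17.8 was used to calculate the optimal sample size", applied to both arms. Part 1 has 80, 120, 80 and 120 patients in Con, T1, T2 and T3; Part 2 has 100 in each of four arms.

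The Statistical analysis section gives the general rule that "analyses of variance (ANOVAs) will be used for normally distributed variables", with the Kruskal–Wallis test otherwise. The switch depends on normality, not on spread. The Primary/secondary efficacy endpoints section sets an ANCOVA for the primary endpoint with treatment, baseline and site. Neither section mentions unequal variances, and neither names pairwise contrasts or confidence intervals.

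**The concern.** The authors saw that the two pilot arms differ in spread and allowed for it when sizing the trial. The analysis does not carry this through. Standard ANOVA and ANCOVA estimate one error variance over all four arms. If the arms differ, that estimate is too large for contrasts between low-variance arms and too small for contrasts between high-variance arms.

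The trial's questions are contrasts. By Table 1, T3 and T1 differ only in postoperative TEAS, and T3 and T2 only in intraoperative TEAS. The sample size rests on sham against all-phase TEAS, that is, Con against T3. At stake is whether the error rates and interval widths for these comparisons are as stated.

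**Working it through.** **Inputs.** Sample size calculations section: SDs 9.8167 h and 17.8499 h, difference 8.762 h, Part 1 group sizes 80/120/80/120. Statistical analysis section: "Statistical significance for this study is defined as α = 0.05 for a two-sided test". The SDs of T1 and T2 are not given; I assume 9.8 to 17.8 h. Covariate adjustment is ignored.

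**The plan's own figure.** The text says "In Part 1, according to a ratio of 3:2 and a power of 90%, a total of 110 and 73 patients were needed per group". With a common SD of 17.8, the smaller group needs (1 + 1/1.5) × 17.8² × (1.960 + 1.282)² / 8.762² = 72.3, so 73; the larger needs 1.5 × 73 = 109.5, so 110. The figure reproduces.

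**Variance ratio.** 17.8499² / 9.8167² = 318.62 / 96.37 = 3.3.

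**Formulas.** MSE = Σ(nᵢ − 1)SDᵢ² / 396. Pooled SE = √[MSE(1/nᵢ + 1/nⱼ)]. True SE = √(SDᵢ²/nᵢ + SDⱼ²/nⱼ). True alpha ≈ 2[1 − Φ(1.966 × pooled SE / true SE)].

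**Worked case: Con 9.82 h, all TEAS arms 17.85 h.** MSE = (79 × 96.37 + 317 × 318.62)/396 = 274.3.
- T3-Con: √[274.3(1/120 + 1/80)] = 2.390 against √(318.62/120 + 96.37/80) = 1.965; ratio 1.22.
- T3-T1: √(274.3 × 2/120) = 2.138 against √(318.62 × 2/120) = 2.304; ratio 0.93.

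**Range over the unknown SDs, T1 and T2 alike** (ratio, with true alpha in brackets):

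| SD of T1 and T2 | MSE | T3-Con | T3-T1 | T3-T2 |
|---|---|---|---|---|
| 17.85 h | 274.3 | 1.22 (1.7%) | 0.93 (6.8%) | 0.93 (6.8%) |
| 13.8 h | 210.2 | 1.07 (3.6%) | 0.91 (7.4%) | 0.93 (6.7%) |
| 9.82 h | 163.2 | 0.94 (6.5%) | 0.89 (8.1%) | 0.94 (6.5%) |

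Over all six contrasts the ratios span 0.93 to 1.22, 0.91 to 1.25 and 0.89 to 1.30, so errors in both directions occur in each case. If T1 and T2 differ from each other, the range widens. With T1 at 17.85 h and T2 at 9.82 h, MSE = (158 × 96.37 + 238 × 318.62)/396 = 229.9, and T3-T1 is 0.85 while T3-T2 is 1.11. With the two reversed, MSE = 207.5, and they are 1.00 and 0.81.

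**Overall test.** The simulated type I error of the four-group ANOVA (20,000 runs each) is 4.6%, 4.4% and 4.6% for the three rows.

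**Power at 8.762 h**, with 72 and 108 completers after 10% loss and the SDs of the worked case: pooled SE 2.520, true SE 2.071. With the pooled error, Φ[(8.762 − 1.967 × 2.520)/2.071] = 96.7%. With group-specific variances, 98.8%.

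**Role of the allocation.** With 100 in every arm and the SDs of the worked case, MSE = (96.37 + 3 × 318.62)/4 = 263.1. T3-Con is then √(2 × 263.1/414.99) = 1.13 and T3-T1 is √(263.1/318.62) = 0.91. The mixed error remains without any imbalance.

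**Part 2.** The arm SDs are unknown. If they are equal, nothing changes. If they were 9.8, 9.8, 17.8 and 17.8 h, the contrasts of either active arm with Con′ or T1′ would be exact, Con′-T1′ 47% too wide and T2′-T3′ 19% too narrow, with an overall type I error of about 6.1%.

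**The case against.** The strongest reply is that the article commits to no contrast that goes wrong. It states an overall comparison, which keeps its size in Part 1, and the variance structure may be set in an analysis plan that is not shown. If each pair were tested with its own two-group error, T3-Con would be 11% too wide and no contrast would be too narrow in the three tabulated cases. This stands, and it makes the point conditional. It does not remove it: the two named methods assume a common variance in standard form, and the only stated alternative responds to non-normality.

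The variance gap may also be partly chance. The SDs come from two arms of a single-center pilot of unstated size. A ratio of 1.82 would give p of about 0.09 with 10 patients per arm and about 0.03 with 15. This also stands.

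A reader might infer that the sized comparison, T3 against Con, necessarily loses power. The documents do not support that. The direction depends on the unknown SDs of T1 and T2, and at the design difference the loss is about 2 points, with both values above the planned 90%. A large loss, such as 51% against about 67% power, appears only for a 5 h effect, which the article nowhere mentions. A reader might also blame the 80/120 allocation, but it applies to Part 1 only and is not the main cause.

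**Conclusion.** The point holds in conditional form and is minor to moderate. It rests on three assumptions: the pilot SDs carry over to Part 1, contrasts use one error pooled over four arms, and T1 and T2 share an SD between the two pilot values. Nominal 5% contrasts then have a true alpha of about 6.5 to 8% for T3-T1 and T3-T2, and from 1.7 to 6.5% for T3-Con. The cause is pooling unequal variances. The overall Part 1 test and the power at the design difference are not in question. For Part 2 no size can be given: every arm receives preoperative and intraoperative TEAS, so the all-sham pilot SD has no direct counterpart there.

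**What to change.** Fit the ANCOVA with a separate residual variance for each treatment group, or keep the model and use heteroscedasticity-consistent standard errors. Where plain ANOVA is used for continuous outcomes, use Welch's test and Welch contrasts. Prespecify this for Part 2, which the Trial status section describes as still recruiting. The same section says that Part 1 has been analysed, so report it there as a sensitivity analysis beside the analysis already done.

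The cost is about one line of SAS code and slightly fewer degrees of freedom. If the variances prove equal, the results are practically unchanged.
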